#### 6.3.4 Analysis related to secondary objective

##### *6.3.4.1 Mechanical ventilation at day 28.*

The percentage of patients requiring mechanical ventilation at 28 days after the start of treatment. The comparison of these proportions would be done by chi-square test, with significance level 0.05 and presentation in the form of absolute risk reduction, relative risk reduction and number needed to treat, with their respective 95% confidence intervals.

---

#### 6.3.4.2 Overall mortality

Overall mortality will be analyzed at the end of the follow-up period. This endpoint will be analyzed as for time to mechanical ventilation.

#### 6.3.4.3 Mortality at 48h, 7 days, in ICU and in hospital

Mortality at 48h, 7 days, in ICU and in hospital will be analyzed at the end of the follow-up period. This endpoint will be analyzed as for time to mechanical ventilation.

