## 2.2 Study rationale

As shown by the data available in the most recent literature generated from the Chinese experience, and by the most recent data made available by the different Spanish hospitals responsible for the management of these patients, hyper- inflammation, caused by a cytokine storm resulting from an exaggerated response of the immune system to the presence of the virus (CSS-like pneumonia), is considered to represent one of the most important negative prognostic factor in patients infected with SARS-CoV-2. The inclusion criteria for COVID-19 used in this protocol is based on the analysis of routine blood chemistry data obtained from patients with SARS-CoV-2 infection. This criterion has been designed with high sensitivity (>90%) for patients who require ICU admission (12). This constitute the rationale for testing drugs specifically targeted to reduce the cytokine storm.

This protocol has been prepared for the purpose of addressing the current medical emergency, given the severity of the disease and the extremely high number of individuals affected. The objective of this study is to investigate anakinra to reduce the number of patients requiring mechanical ventilation. This is intended to address the most urgent need to preserve the access to intense care unit support to the lower possible number of patients and may potentially reduce mortality.

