## 6.2 Definition of study populations

All efficacy and safety analyses will be conducted on the all Treated population which will comprise all randomized patients receiving study treatment.

Patients will be included in the groups to which they were randomized for all evaluations of efficacy and in the groups according to treatment received for all evaluations of safety.

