#### *6.3.3.2 Secondary endpoints supporting the primary objective*

##### Time to mechanical ventilation

Analysis of the time to mechanical ventilation from the point of randomization will be undertaken by plotting Kaplan-Meier curves for each of the 2 treatment groups and by pairwise comparisons (anakinra versus standard of care) using the log rank test. Hazard ratios will be estimated using the Cox proportional hazards model and these will be presented together with 90% two-sided confidence intervals.

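### In-ICU and in-hospital mortality are assigned a Kaplan-Meier, log-rank and Cox analysis that does not treat live discharge or death elsewhere as a competing event

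*Protocol*

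**What the plan says.** Section 3.2.1 lists mortality at 48 hours, at 7 days, in the ICU and in hospital as secondary endpoints, next to total mortality at Day 28. It gives no denominator for the ICU and hospital items.

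Section 6.3.4.3 takes all four together: "Mortality at 48h, 7 days, in ICU and in hospital will be analyzed at the end of the follow-up period". The next sentence assigns the method: "This endpoint will be analyzed as for time to mechanical ventilation".

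That method is set out in section 6.3.3.2. It begins: "Analysis of the time to mechanical ventilation from the point of randomization will be undertaken by plotting Kaplan-Meier curves". It goes on to "pairwise comparisons (anakinra versus standard of care) using the log rank test", and then: "Hazard ratios will be estimated using the Cox proportional hazards model and these will be presented together with 90% two-sided confidence intervals". Neither section mentions live discharge, leaving the ICU alive, or death in another place, either as censoring or as a competing event.

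The analysis set is fixed in section 6.2: "All efficacy and safety analyses will be conducted on the all Treated population which will comprise all randomized patients receiving study treatment". For efficacy, patients stay in the arm to which they were randomised. Section 6.3.1 makes the secondary endpoints descriptive and any p-values exploratory.

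**The concern.** The assigned method suits an event that every patient under follow-up can still have. All-cause death is such an event. Death in hospital is not, because a patient sent home alive has left the place in which the event is counted. For death in the ICU, the same holds for a patient who dies on the ward or goes home without dying in the ICU.

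The common handling is to censor at the exit. Kaplan-Meier then assumes that the discharged patient would have gone on dying in hospital at the same rate as those still admitted. That is implausible here, because section 4.1 ties discharge before Day 15 to sufficient improvement. Exits therefore carry information about prognosis. They may also differ between arms, since section 2.2 gives the purpose as follows: "The objective of this study is to investigate anakinra to reduce the number of patients requiring mechanical ventilation".

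At stake are the size of the reported in-hospital and in-ICU mortality in each arm, and the visibility of any benefit that comes through faster recovery. Mortality is the trial's secondary objective (section 3.2), so these figures will be read with attention even though they are descriptive.

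**Working it through.** The protocol gives no figure for these endpoints, so there is none to reproduce. The check has two parts: what method applies, and how far it can mislead.

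**Method that applies.** Section 6.3.4.3 refers to section 6.3.3.2, which gives Kaplan-Meier from randomisation, a log-rank test and a Cox hazard ratio with a 90% interval. The analysis set is all randomised patients receiving study treatment (section 6.2). No competing event is named in either place.

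**Illustration.** All rates are assumptions; none comes from the protocol. Hazards are constant: death in hospital h_d per day, live discharge h_r per day, horizon t = 28 days.

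- Kaplan-Meier with discharges censored: 1 − exp(−h_d·t)
- Actual probability of dying in hospital: h_d/(h_d + h_r) × [1 − exp(−(h_d + h_r)·t)]

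With h_d = 0.01 and h_r = 0.08:

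- Kaplan-Meier: 1 − exp(−0.28) = 24.4%
- Actual: (0.01/0.09) × [1 − exp(−2.52)] = 10.2%

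The Kaplan-Meier figure is about 2.4 times the actual one (24.4/10.2).

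**Range, and effect on the comparison.** Take the same death hazard in both arms, control discharge at 0.06 per day, and faster discharge on anakinra:

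| h_d (both arms) | Kaplan-Meier (both arms) | Actual, control (discharge 0.06) | Actual, anakinra (0.09) | Actual, anakinra (0.12) | Actual risk ratio |
|---|---|---|---|---|---|
| 0.004 | 10.6% | 5.2% | 3.9% | 3.1% | 0.76 to 0.60 |
| 0.006 | 15.5% | 7.7% | 5.8% | 4.6% | 0.76 to 0.60 |
| 0.010 | 24.4% | 12.3% | 9.4% | 7.5% | 0.77 to 0.61 |

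In every row the Kaplan-Meier curves of the two arms coincide and the Cox hazard ratio is 1.0, because discharge enters neither. The control-arm level is overstated about twofold. A real reduction of roughly 23% to 40% in the risk of dying in hospital does not show at all.

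**If exits are not censored.** Suppose instead that every discharged patient is kept in the risk set, event-free, until Day 28, and follow-up is complete. Kaplan-Meier then equals the simple proportion (10.2% in the first example) and the gap vanishes. The size of the problem therefore depends wholly on a handling rule that these sections do not state.

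**The case against.** The strongest reply is that censoring at discharge is nowhere written. Section 4.1 continues follow-up after discharge, by telephone or in person, to the end of the study. Table 3 and section 4.5.3.7 collect survival and discharge. A patient sent home can therefore be carried event-free to Day 28, and censoring rules are commonly left to a statistical analysis plan, which is not shown here. This stands as far as it goes: the 24% against 10% is conditional on the usual handling and on assumed rates. It does not dispose of the point. The protocol itself fixes the method for these endpoints, and that method gives the right answer only if exits are specially handled.

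A reader might also infer that in-ICU mortality will be computed among ICU patients only, which would condition on an admission that happens after randomisation. That could reverse a result. For example, with assumed ICU admission of 15% against 8% and ICU deaths of 6% against 4% of all patients, mortality per ICU patient is 0.06/0.15 = 40% against 0.04/0.08 = 50%. The documents do not support this reading. The inherited method runs from randomisation, section 6.2 uses all randomised treated patients, and no ICU-only set is defined. The example is a reason to rule such a comparison out explicitly. It is not a defect of the plan as written.

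It is also fair to say that no decision rests on these endpoints. They are descriptive under section 6.3.1, and total mortality at Day 28 is not tied to a place.

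**Conclusion.** The point holds in a limited form. For in-ICU and in-hospital death, section 6.3.4.3 assigns a method that does not treat live discharge, or death outside the ICU or hospital, as a competing event. If these exits are censored in the usual way, in-hospital death is overstated by a factor of about 2 to 2.4 at the rates assumed above, and a difference between arms that works through faster discharge is missed. These sizes rest on constant hazards and on rates chosen for illustration.

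It would go too far to say that the trial's mortality results as a whole are compromised. Mortality at 48 hours, at 7 days and at Day 28 from any cause does not depend on place and does not share the problem. Nor does the protocol state that discharged patients are censored, or that only ICU patients are at risk. The consequence is moderate, but the correction is easy and should be made.

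**What to change.** Reword section 6.3.4.3 as follows:

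- Keep all patients of the analysis population, in their randomised arm, as the denominator for every mortality endpoint.
- Report in-ICU and in-hospital deaths as proportions by Day 28. Alternatively, report them as cumulative incidence, with live discharge and death elsewhere as competing events.
- State that no comparison between arms will be restricted to patients admitted to the ICU.
- Read 48-hour and 7-day mortality from the single all-cause survival curve.
- Name Day-28 all-cause mortality as the lead mortality result.

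The cost is analysis wording only. Survival and discharge are already collected (Table 3, section 4.5.3.7), and neither the sample size nor the visit schedule changes.

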#### 6.3.4.4 Adverse events

Reported AEs during the study will be coded using MedDRA. The incidence of AEs will be summarized in frequency tables by treatment, system organ class, preferred term and maximum severity. Separate tabulations will be performed for serious and non-serious AEs.

### 6.3.5 Analysis related to exploratory objective

#### Change from baseline in hyperinflammatory parameters

Change from baseline during treatment until Day 15 with measurements performed days 1, 4, 7 and 15 of the following parameters will be summarized using descriptive statistics:

- Ferritin
- LDH
- D-dimers
- CRP

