### 3.3 Exploratory objective

To assess the effect of anakinra on IL-6, ferritin, and selected biomarkers relevant for hyperinflammation, MAS and cytokine storm change from baseline.

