#### 3.3.1 Exploratory endpoints

- Change (improvement) in IL-6, ferritin, D-dimer, TGs, lymphopenia, CRP, ESR, LDH.
- Time to defervescence (fever end)

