#### 4.5.3.6 Laboratory assessments

Blood samples for determination of the laboratory assessments described in Table 4 will be drawn at Visits 1 to 4. The date and time of blood sampling will be recorded in the CRF.

Table 4 Laboratory assessments:

|                                                                                          |                                            |
|------------------------------------------------------------------------------------------|--------------------------------------------|
| Biochemistry                                                               | Hematology                   |
| Aspartate aminotransferase (AST)                                                         | Hemoglobin                                 |
| Alanine aminotransferase (ALT)                                                           | ESR                                        |
| Total bilirubin (if >upper limit of normal also conjugated and non-conjugated bilirubin) | Platelet count                             |
| Prothrombin Time/International Normalized Ratio (PT-INR)                                 | White blood cells                          |
| Fibrinogen                                                                               | RBC                                        |
| Cardiac troponin                                                                         | Differential blood count                   |
| Creatinine                                                                               | Hyperinflammatory parameters |
| C-reactive protein (CRP)                                                                 | Ferritin                                   |
|                                                                                          | LDH                                        |
|                                                                                          | D-dimers                                   |
|                                                                                          | IL-6                                       |

All laboratory samples will be analyzed at the respective local hospital laboratory according to their standard routines.

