#### *4.5.5 Exploratory assessments*

Blood samples for determination of IL-6 and selected exploratory parameters will be collected at Day 1, 7 and 15, whenever possible. The date and time of sampling will be recorded in the CRF.

All samples will be analyzed at the respective hospital local laboratory according to their standard routines.

---

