## 6 Statistical plan

### 6.1 Determination of sample size

The study will enroll a total of 180 patients, 90 per arm according to the 1:1 randomization. The sample size has been estimated based on the following assumptions:

- The sample size is calculated in based of the data collected in the database of COVID-19 of the Complejo Hospitalario de Navarra , which currently has a total of 188 patients. After the analysis of the data, it is estimated that 15% of severe pneumonia COVID patients have required mechanical ventilation.
- For and Type I error of 0.05 and a power of 75% for each comparison under the assumption that the true success rates are 88% in the SoC group increasing to 92% in the anakinra group.
- It is needed 180 patients (90 per arm) considering a loss of 10%.
- The study will consist of two stages, with equal numbers of patients randomised into Stage 1 (treatment) and into Stage 2 (follow-up) per treatment arm.

The calculations on the operating characteristics of this design have been undertaken using the website of Sample size calculator of *National Center for Advancing Translational Sciences, National Institutes of Health*, through [UCSF-CTSI](#) , Software utilities developed by [[contact]](mailto:[contact]), last up to date version on April 14, 2020.

The value for the type I error has been chosen in recognition of the urgent unmet medical need to allow the identification of a signal, at least, from a statistical perspective. Having seen a statistical signal, it is then a matter of evaluating whether the observed treatment differences represent clinically relevant effects that can satisfy that unmet need.

In case indications of efficacy requires to be confirmed, additional patients may be added into this study.

In case the outcome is statistically convincing, efficacy will be considered confirmed and the results will, where warranted, be used to seek regulatory approvals.

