### 6.3.1 General statistical issues

This design has acceptable properties in terms of the false positive potential, controlling the overall type I error at 5%, for each of the two treatment comparisons.

Secondary endpoints will be evaluated in a descriptive way. In some cases, p-value comparisons will be undertaken, but these are to be interpreted in an exploratory way.

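### Section 6.3.5 gives no between-arm estimate for the inflammatory markers and leaves out IL-6, ESR and triglycerides, so it does not answer the exploratory objective

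*Protocol*

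**What the plan says.** Section 3.3 states the aim: "To assess the effect of anakinra on IL-6, ferritin, and selected biomarkers relevant for hyperinflammation, MAS and cytokine storm change from baseline". Section 3.3.1 turns it into an endpoint: "Change (improvement) in IL-6, ferritin, D-dimer, TGs, lymphopenia, CRP, ESR, LDH".

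The matching analysis is 6.3.5. Its first list is introduced by "Change from baseline during treatment until Day 15 with measurements performed days 1, 4, 7 and 15 of the following parameters" and contains ferritin, LDH, D-dimers and CRP. Its second list covers other laboratory values, including white cells with differential count. Both are handled the same way: the values "of the following parameters will be summarized using descriptive statistics". Neither list mentions a comparison of arms, a confidence interval or a model.

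On sampling, 4.5.3.6 says the blood samples for Table 4, which includes IL-6 and ESR, "will be drawn at Visits 1 to 4". Section 4.5.5 says: "Blood samples for determination of IL-6 and selected exploratory parameters will be collected at Day 1, 7 and 15, whenever possible".

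The general rule in 6.3.1 is "Secondary endpoints will be evaluated in a descriptive way", with some p-values to be read as exploratory. It does not mention the exploratory endpoints.

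**The concern.** Damping the cytokine storm is the mechanistic rationale of the trial (2.1 and 2.2), and the marker data are where that rationale can be examined. The objective asks what anakinra does to the markers, which is a question about the difference between randomised arms. The plan supplies only the course of each marker over time.

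A fall within the anakinra arm has at least three possible sources: the drug, natural recovery, and regression to the mean. The last is plausible because 4.3.1 admits patients with at least one of IL-6, ferritin, CRP or LDH above a cut-off. The endpoint wording, which equates change with improvement, invites the within-arm reading. Only the contrast with standard of care separates these sources.

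IL-6, the first marker named in both the objective and the endpoint, has no planned analysis at all. If 6.3.5 is followed as written, the report contains nothing on it.

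**Working it through.** **Marker lists side by side**

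| Marker in 3.3.1 | In Table 4 | In 6.3.5 |
|---|---|---|
| IL-6 | yes | no |
| Ferritin | yes | first list |
| D-dimer | yes | first list |
| Triglycerides | no | no |
| Lymphopenia | yes, through the differential count | second list, through the differential count |
| CRP | yes | first list |
| ESR | yes | no |
| LDH | yes | first list |

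Three of eight have no analysis. Two of those three are collected; triglycerides are neither scheduled in Table 4 nor analysed.

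**Sampling days for IL-6**

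- Section 4.5.3.6 with Table 4: Visits 1 to 4, which Table 3 dates as Days 1, 4, 7 and 15.
- Table 3, biomarker row: the same four days.
- Section 4.5.5: Days 1, 7 and 15 only, and only where feasible.
- Section 6.3.5: Days 1, 4, 7 and 15. Adding IL-6 to its first list unchanged would import the Day 4 conflict.

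**Efficiency of the use of baseline**

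The plan has no sizing or precision figure for the markers, so there is none to reproduce. The only sample size in the document is for the primary endpoint: "The study will enroll a total of 180 patients, 90 per arm according to the 1:1 randomization". Whether that size suits the primary endpoint is a separate question. Here it only supplies n. With the 10% loss in 6.1, n = 90 × 0.9 = 81 per arm.

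The protocol gives no SD and no baseline-to-follow-up correlation ρ. I assume ρ from 0.3 to 0.7, on the log scale, with SD 1 at both times.

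- Per-patient variance of raw change: 2(1 − ρ).
- Per-patient variance after covariate adjustment, large samples: 1 − ρ².
- Ratio: (1 − ρ²) / [2(1 − ρ)] = (1 + ρ)/2.
- Half-width of the 95% CI for the arm difference: 1.96 × √(2 × variance / 81), in SD units.

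| ρ | Raw change | Adjusted | Ratio | Variance cut | Half-width, change | Half-width, adjusted |
|---|---|---|---|---|---|---|
| 0.3 | 1.40 | 0.91 | 0.65 | 35% | 0.364 | 0.294 |
| 0.5 | 1.00 | 0.75 | 0.75 | 25% | 0.308 | 0.267 |
| 0.7 | 0.60 | 0.51 | 0.85 | 15% | 0.239 | 0.220 |

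Widening the range to ρ = 0.2 and 0.8 gives cuts of 40% and 10%.

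The direction does not depend on equal SDs. If the follow-up SD is k times the baseline SD, raw change has variance 1 + k² − 2ρk and the adjusted analysis k²(1 − ρ²). The difference is (1 − ρk)², which is never negative. In large samples adjustment is therefore never the less precise choice.

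**The case against.** The strongest reply is that nothing here is out of line for an exploratory endpoint. The endpoint is defined as change, and 6.3.5 summarises change. Even secondary endpoints are mainly descriptive, and a statistical analysis plan that is not shown may add a model. This stands as far as severity goes. It does not remove the mismatch of lists: 6.3.5 fixes named parameters, and they do not match 3.3.1. Nor can a reader recover the contrast from by-arm tables of mean, SD and range if the comparison belongs on the log scale.

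Several stronger readings are tempting, and the documents do not support them.

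- *The plan ignores baseline.* It does not; change from baseline subtracts it. What is absent is adjustment for it as a covariate.
- *Every patient has a baseline value for every marker.* Day 1 laboratory work is scheduled, but 4.5.5 makes IL-6 and selected parameters conditional on feasibility.
- *Regression to the mean guarantees improvement, or biases the trial.* D-dimer is not an entry criterion, and one raised marker is enough for entry. Eligibility may rest on results already in the records (4.5.1.2), so some regression can occur before the Day 1 baseline. Randomisation makes it equal in expectation between arms, so a contrast of arms is not biased by it. The weakness lies only in reading change within one arm.
- *Power is being lost.* For an assumed 0.4 SD effect, 81 per arm and ρ = 0.5, a change-score test would have 72% power and an adjusted one 84%. Section 6.3.5 plans no test, so those 12 points are not a loss under this plan.

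**Conclusion.** The point holds and is minor. Section 6.3.5 does not deliver what 3.3 and 3.3.1 ask for, in two respects: three of eight named markers have no analysis, and no marker has an estimate of anakinra against standard of care. The first is an internal inconsistency visible on the page and rests on no assumption. It may well be clerical, since Table 4 groups IL-6 with the hyperinflammatory parameters.

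The gain from baseline adjustment is real, but its size rests on a correlation that the protocol does not give: a 35% to 15% cut in variance for ρ of 0.3 to 0.7, assuming equal SDs and 81 patients per arm for the half-widths. If ρ is high the gain is small. Samples missed, deaths and discharges would reduce n below 81. No confirmatory conclusion depends on any of this.

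**What to change.** - Add IL-6 and ESR to 6.3.5. Either drop triglycerides from 3.3.1, or add them to both Table 4 and 6.3.5.
- Reconcile Day 4 sampling of IL-6 across Table 3, 4.5.3.6, 4.5.5 and 6.3.5.
- For each marker, report an anakinra versus standard-of-care contrast (a ratio of geometric means) with a 95% CI. Take it from a linear model of the log value on arm and log Day 1 value, at one prespecified time point, labelled exploratory. Day 7 is one reasonable choice: it is in both sampling schedules and is likely to be less depleted by discharge and death than Day 15, though the protocol gives no figures to settle this.
- State how many patients contribute to each estimate, since 6.3.8 rules out filling in missing values.
- Keep the descriptive tables.

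The cost is a paragraph of analysis text, one model per marker and small edits to the lists and schedule. Apart from triglycerides, if they are kept, no new measurements are needed. The downside is a few more exploratory estimates to report, and an IL-6 estimate that will rest on incomplete samples.
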